#### Outcome measures

We will be collecting data using viral load results (at month 4 and month 12—obtained from patient records and the National Health Laboratory Service online system), EAMs (daily), pharmacy refills (monthly), and participant and staff surveys. The primary outcome will be viral suppression at month 24 post-enrollment as measured by plasma HIV-1 viral load <50 copies/mL. Secondary outcomes will include viral suppression at month 12, change in viral load over time, and total days of unsuppressed virus during study participation. Additional secondary outcomes include the following: mean electronic adherence and percent of participants ≥90% and ≥80% adherence in months 12 and 24; mean adherence over months 1–12 and 1–24; retention in ART care (percent of participants attending all refill visits within 7 days for monthly refills and 14 days for longer refill intervals) over months 1–12 and 1–24; percent of participants attending ≥75% refill visits (within 7 days), over months 1–12 and 1–24; percent of participants lost to care, defined as no clinic contact for ≥12 weeks at month 24); and time to suboptimal adherence detection and linkage to support (number of days from month 0 to day identified as nonadherent, as per the definition used in their intervention; number of days from month 0 to linkage to ROTF support).

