There are several methods of adherence monitoring and ways of identifying people who need extra support—each with its own strengths and weaknesses. The current standard for monitoring adherence in South Africa is through self-report, which is often unreliable [2], and through infrequent viral load measurements, recommended at 4 and 12 months after initiating ART and annually thereafter [26]. However, feedback of the viral load result to the patient is often only given at the next routine clinic visit, resulting in a delay in initiating adherence support measures. Electronic adherence monitors (EAM) that track adherence in real time are acceptable and feasible in many settings and have been used to deliver reminders and trigger just-in-time support [27–32]. In HIV treatment, the benefit-cost ratio of broad use of EAM in clinical settings is unknown. Another method that leverages existing infrastructure is pharmacy refill monitoring (PRM). PRM data can detect suboptimal adherence after a missed refill, prior to viral load becoming unsuppressed [2, 33]. A third approach is early patient outreach when unsuppressed virus is detected. Early outreach is not done in most resource-limited settings, but is feasible and well-liked by patients [34].

This study’s primary research goal is to identify the optimal combination of evidence-based and scalable HIV interventions for resource-limited, high-burden settings. In Cape Town, health officials have established Risk of Treatment Failure (ROTF) clinics, where patients with unsuppressed virus receive extra support via (a) one nurse-led counselling session and (b) peer counselling (3–4 sessions) [35]. Our hypothesis is that the test we have designed will allow us to identify a superior combination of interventions. Thus, working in collaboration with the City of Cape Town, we plan to (1) test the relative contributions of five promising intervention components, three comprising adherence monitoring methods, and two comprising extra support elements; (2) collect cost and other implementation data; and (3) optimize a multi-component intervention package with high levels of cost-effectiveness and characteristics identified as necessary for implementation success.

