#### Timeline

Participants will be enrolled for a total of 24 months, with study follow-up visits at months 4, 8, 12, 18, and 24 (Fig. 1). The intervention components will be applied for the first 12 months of enrollment.

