#### Data and statistical analysis

Study staff will collect data directly onto the REDCap database using password-protected tablets. The REDCap database was designed with automated internal checks to ensure data entered are accurate and complete. In addition, the site follows a data management plan, which outlines quality control and quality assurance practices. All participants will be assigned a study identifier and data for analysis will only be identified through this number. All documents that contain personal identifiers will be kept in locked cabinets with limited access.

We will employ a series of descriptive and inferential statistical methods and techniques for data analysis. For dataset preparation, missing baseline data on socio-demographics will be imputed using a single imputation technique if the proportion missing is <10% or using a multiple imputation technique if the proportion missing is ≥10%, respectively. In cases of missing viral load data, we will treat the result as detectable, in accordance with our primary intention-to-treat (ITT) analytic approach, similar to other studies [3, 63]. For missing adherence data, the most recent month’s adherence will be used to estimate single-month adherence; for cumulative calculations, available data over the period will be used.

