To estimate treatment effects, we will adopt an ITT analytic approach and all 512 participants will be analyzed according to their randomized condition. The primary outcome is viral suppression at 24 months (see Table 1), measured as a binary variable, to allow us to assess a sustained post-intervention effect [64]. We will use logistic regression to estimate main and interaction effects on the odds of viral suppression. We will use an exchangeable correlation matrix, accounting for clustering by health facility for all analyses. Participants’ receipt of intervention components will be effect-coded. That is, following Kugler et al., [65] we will code participants’ receipt of an intervention component as 1, and nonreceipt as −1. To estimate the main effect of an intervention component, we will multiply the coefficient term by two and exponentiate it (i.e., implementing the mathematical operation as follows: Exp(2*coefficient term)). We will use the same approach to estimate interaction effects between components. Similarly, we will use logistic regression to estimate effects of components on secondary outcomes measured as a binary outcome (viral load at month 12; adherence; retention). We will use linear or Poisson regression to estimate effects of components on outcomes measured as a continuous variable (e.g., mean change in viral load from month 0 to 12 and month 0 to 24) or count variable (e.g., days of unsuppressed virus), respectively. We will compare dropout rates and characteristics of participants who drop out or are lost to follow-up with those retained to assess potential for bias. We will also assess evidence of contamination by examining data from our detailed REDCap records and texting logs, using any such evidence when interpreting data on outcomes. Moderating effects will be explored through regression modeling following Hayes [66]; mediators will be assessed using the approach by Valeri and VanderWeele, which allows for logistic modeling, and sensitivity analyses will be conducted on key assumptions per Imai [67, 68]. For all quantitative analyses, we adopted REDCap for data capture and SAS for data analysis [69].

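### Time to detection and time to ROTF linkage are days to an event that many participants will never have, and no stated model handles participants without the event

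*Protocol article*

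**What the plan says.** Under Outcome measures, the protocol article lists time to detection and linkage to support among the secondary outcomes. The first is the "number of days from month 0 to day identified as nonadherent, as per the definition used in their intervention"; the second is the "number of days from month 0 to linkage to ROTF support". No value or censoring rule is given for a participant who never reaches the event. The Background describes the ROTF clinics as places "where patients with unsuppressed virus receive extra support", so a participant who stays suppressed need not be linked at all.

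Data and statistical analysis assigns models by type of measurement. For binary secondary outcomes, "we will use logistic regression to estimate effects of components on secondary outcomes measured as a binary outcome". For the rest, "We will use linear or Poisson regression to estimate effects of components on outcomes measured as a continuous variable" or a "count variable (e.g., days of unsuppressed virus), respectively". The two time outcomes are not named, and no time-to-event method appears. The same section commits to intention to treat, with all 512 participants analysed as randomised. Its missing-data rules cover baseline data, adherence and viral load ("In cases of missing viral load data, we will treat the result as detectable"); none covers a participant who is never detected or never linked.

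Under Timeline: "The intervention components will be applied for the first 12 months of enrollment". Follow-up lasts 24 months.

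**The concern.** The outcome exists only for participants who have the event. Someone found non-adherent on day 122 scores 122; someone adherent and suppressed throughout scores nothing. If a linear or Poisson model is fitted to the days that exist, the second person is left out. Whether a person is detected is itself a consequence of the monitoring components, so the people left at the on and off levels of M1, M2 or M3 are no longer the groups that randomisation made comparable.

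These outcomes are meant to show whether monitoring finds trouble sooner, which is the trial's rationale for M1 to M3. The Blinding section says all analyses are unblinded. A later choice between excluding never-detected participants, giving them the last day, or censoring them would therefore be made with allocation visible, and the three can give very different answers.

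**Working it through.** The article gives no power figure or expected number of events for these two outcomes, so there is no figure of the plan's to reproduce. The check asks what a detected-only analysis would do.

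**Inputs from the article.** Each component is on in 8 of 16 conditions of 32, so 256 v 256. Components run 12 months (T = 365 days). Two-sided alpha is 0.05. Planning suppression of 60% and 74% implies 40% and 26% unsuppressed, a rough anchor for detection by viral load only.

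**Assumptions, not in the article.** The share p detected by day 365 at the off level is 20-40%, the detection hazard is constant, and the component doubles it.

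**Step 1: constant hazard.** The hazard is λ = −ln(1−p)/T. Among the detected:

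- mean = 1/λ − T·e^(−λT)/(1−e^(−λT))
- variance = 1/λ² − T²·e^(−λT)/(1−e^(−λT))²

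At p = 30%:

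- Off level: 1/λ = 1023.3, so the mean is 1023.3 − 365×0.70/0.30 = 171.7 days (SD 105.0).
- On level, with 2λ: 51% are detected and the mean is 511.7 − 365×0.49/0.51 = 161.0 days (SD 104.0).
- Numbers detected: 256×0.30 = 76.8 and 256×0.51 = 130.6, so about 305 of 512 are not analysed.
- SE = √(105.0²/76.8 + 104.0²/130.6) = 15.05, and z = 10.7/15.05 = 0.71.
- Detected-only power = Φ(0.71−1.96) + Φ(−0.71−1.96) = 10.9%.
- Log-rank on all 512, with 207.4 events: Φ(ln2·√(207.4/4) − 1.96) = Φ(3.03) = 99.9%.

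| Detected, off v on | Mean days among detected | Not analysed | Power, detected-only | Power, censored |
|---|---|---|---|---|
| 20% v 36% | 175.7 v 169.0 | 369 | 6.6% | 98.6% |
| 30% v 51% | 171.7 v 161.0 | 305 | 10.9% | 99.9% |
| 40% v 64% | 167.0 v 152.0 | 246 | 21% | over 99.9% |

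Simulated Weibull times (shapes 0.6 and 1.5) give similar detected-only power, 6-23% over the same range. With more detection the loss shrinks: 66% power at 60% detected and 90% at 70%.

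**Step 2: the stated schedules instead.** Table 1 has routine viral loads at months 4 and 12, refill checks monthly or two-monthly, and electronic monitoring reviewed weekly. Take onset of non-adherence at a constant rate, reaching 20, 30 or 40% by day 365 at the off level of M3. M2 is on in four of the eight M3-off conditions (Table 2), so let half of that group be found at the next monthly check and half at day 122 or 365. Let the M3 group be found at the next weekly review. Simulated detected-only comparisons (t-test) give:

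- Onset rate doubled with M3: means of about 234, 229 and 226 days off v 173, 165 and 155 on; power 87%, 98% and about 100%.
- Onset rate equal, only check timing different: power about 69%, 84% and 94%.

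The detected-only comparison for M3 can thus be nearly as significant when no more people are detected as when the rate doubles.

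**Step 3: Poisson.** At p = 30% the variance among the detected is 105.0² = 11,025 against a mean of 171.7, a ratio of 64. Model-based standard errors are then too small by a factor of about √64 = 8. In simulation with no effect they rejected in about 78-82% of runs. With robust errors, Poisson behaved like the linear model.

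**The case against.** A reader might infer that the plan excludes never-detected participants. It does not say so. The analysis section assigns neither time outcome to a model, its examples are only examples, and its day-count example (days of unsuppressed virus) is a number that everyone has, possibly zero. The intention-to-treat sentence points away from exclusion. Giving never-detected participants day 365 fits the text equally well. Under Step 1 that keeps power at 95% with 20% detected and at 99% or more from 30%, although it would miscode people lost early.

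A reader might also infer that a doubled detection rate would be almost invisible. That needs a detected-only analysis, a constant hazard and at most about 40% detected. Step 2 removes the constant hazard and gives high power for M3. The 26-40% anchor concerns viral load only; missed refills and doses may flag many more people. Doubling is also not a scenario for every component: M1 acts on the same routine result, and S1 and S2 start only after detection, so they cannot change time to first detection.

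On Poisson, the exchangeable correlation matrix suggests an estimating-equation approach, often used with robust errors, so the false positives are a possibility and not a forecast.

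Finally, censoring rules are usually left to the analysis plan, which is not shown. That answers a complaint of missing detail. It does not fully answer this one: the article itself fixes the outcomes as plain day counts, lists the model families, and promises all 512. Those three statements do not fit together.

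**Conclusion.** The point holds as a mismatch between outcome and method. Both outcomes are days to an event that need not occur, and no stated model can use participants without it. Logistic regression could model whether the event occurred, but not when. Any detected-only or linked-only analysis compares groups selected after randomisation and breaks the commitment to all 512, whatever its power.

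No single figure describes the damage. Under a constant hazard with 20-40% detected at the off level, power for a doubled rate is about 7-21% detected-only against at least 98% with censoring. Under the stated schedules the comparison for M3 can have 87-100% power, much of it from check timing alone. All of these rest on assumed detection shares and onset rates that the article does not give. The outcomes are secondary and the primary analysis is unaffected, so this should be changed but does not threaten the trial.

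**What to change.** Define both outcomes as censored time-to-event variables and analyse all 512 by randomised condition.

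- **Model:** Cox, discrete-time or restricted mean time, with effect-coded components and clinic accounted for. Discrete time suits events that can be seen only at scheduled checks.
- **Censoring:** state the time. For detection, use the end of the 12-month component period or last follow-up if sooner; for linkage, last follow-up. Treat death as a competing event.
- **Reporting:** give the cumulative proportions detected and linked beside the time analysis.
- **Exclude:** state that linear or Poisson models will not be fitted to days among detected or linked participants only.

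The cost is analysis wording and code; the outcome definitions already require the event dates. The change does not cure the separate problem that the detection event follows each condition's own definition. A component comparison will still partly measure the definition and how often it is checked, and that needs its own remedy.

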#### Mediator and moderator variables

Annual surveys will allow us to collect data on SDT constructs (such as autonomy support, motivation, perceived self-competence, social support, and ART knowledge) to test the effect on each in mediating the association between the intervention and outcomes. Further, we will collect data on substance use, depression, gender inequity, stigma, and transport or clinic-related issues to test the extent to which each of these variables independently or in combination moderate the association between the intervention and outcomes.

#### Implementation outcomes

Translation of the optimized intervention into real-world benefits will require a clear understanding of the implementation process. We will assess implementation using a modified Proctor framework (Fig. 3) [52], as this enables measurement of the distinct implementation outcomes in relation to the intervention outcomes, while also considering impact on clients. Brief questionnaires will be administered to all enrolled patients and clinic staff by the study team at two time points during the study to assess both short-term and long-term experiences. A subset of study participants (*n*=30) will also be selected for IDIs to explore acceptability, intervention appropriateness, feasibility, and patient satisfaction further. Clinic observations at each study site will be conducted to assess the fidelity of intervention implementation.

**Fig. 3 Fig3:**
[figure not shown]
Modified Proctor Framework [52]. Abbreviations. Abbreviations. DVL, detectable viral load

#### Costing

A micro-costing analysis will be undertaken to determine the cost of implementing SUSTAIN intervention components and their combinations. Micro-costing is widely used in costing studies [53–55]; it is a bottom-up approach used to estimate the cost of setting up and delivery of an intervention, involving collecting detailed information about the resources required to implement an intervention, and assigning economic unit costs to each component of resource use.

Costs collected will include set-up or non-recurrent unit costs (such as training staff or purchasing materials) and recurrent costs (such as staff salaries). Costs related to research activities will be excluded. We will estimate costs in South African Rand and derive totals in United States Dollars. Intervention costs collected will include equipment, supplies, and services (e.g., text messaging) in accordance with an integrated framework based on the Eaton framework [56] for HIV service delivery and the Saldana framework [57] for costing intervention implementation.

Structured costing forms (log sheets) will be developed and distributed to the study manager and SUSTAIN study staff. During designated periods, study staff will complete individual log sheets to record how much time is spent training each participant to use their EAM devices and conducting counselling. The study manager will also regularly consult with the study coordinator, data clerks/managers, drivers, and other individuals conducting SUSTAIN intervention activities to capture time and costs incurred. We will collect data at multiple time points: pre-study start to collect intervention set-up costs, the first 4 months of study start to capture start-up time and costs, and for an additional 1–2 months in study year 1 and study year 2 to capture steady state costs. Two study investigators will conduct one 2-week time and motion study at each participating clinic once study activities are operating at a steady state to evaluate time needed to conduct each intervention component; these observational data will be used to validate and/or adjust time estimates captured through study staff self-report. All time and cost data will be used to complete intervention cost sheets.

#### Sample size

We anticipate we will need 512 participants for this study to ensure the power to detect a clinically meaningful individual effect of intervention components on HIV viral suppression. Our sample size of 512 combines two estimates: (a) the number of individuals needed to detect a clinically significant sized effect in HIV viral suppression rate due to receipt of an intervention component; and (b) the number of individuals who we may lose over the course of the study. To elaborate, first, we assume we will have a 14-percentage point increase in viral suppression in participants receiving a specific intervention component compared to those who receive the standard of care alone. Our estimate of 14 percentage point increase is based on recent work at Cape Town clinics indicating suppression rates of 51–79% at month 12 post-initiation of ART [4]. Therefore, using the baseline HIV viral suppression rate of 60%, endline rate of 74%, a two-sided alpha of 0.05 and 80% power, and intraclass coefficient component (ICC) of 0.15, we calculated that we will need a sample of 458, using PS Power and Sample Size Calculations [58]. While we do not know the ICC for each clinic to inform the design stage (for the sample size calculation in a RCT design involving participants representing three clinics), we conservatively assumed they are 0.15, based on recent studies showing ICC estimates ranging between 0.01 and 0.12 [59–61]. To account for lost to follow-up of up to 10% (based on site experience in other recent studies), we will need to recruit a total of 510 participants, which we increased to 512 to be able to sample an equal number of participants across three clinics and 16 study conditions. For secondary outcomes, this sample size will allow us to detect differences in ≥90% adherence and in retention of 11–15%, a meaningful range that is reasonable given other studies [22, 62].

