#### Eligibility criteria

Study participants must be adolescents aged 16–17 years or adults ≥18 years of age, who are presenting to the clinic for initiation of ART. Study participants must be willing and able to sign informed consent or, in the case of minors, informed assent with parents willing to sign informed consent. They must have a working cellphone and be willing to receive study-related text messages. They must also be willing and able to comply with study procedures, including using an EAM and providing current contact information. We aim to enroll 512 participants (roughly 170 per clinic) between March 2022 and February 2024.

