#### Randomization

We will randomly assign 512 participants representing three clinics to one of 16 study conditions (Table 2) using a permutation allowing for the study conditions to include an equal number of participants, which is 32 (16*32 = 512). We developed the random assignment of participants in Stata v.14 using *runiform* and *rank* functions. The randomization sequence is concealed from all study staff involved in recruitment, enrollment, and randomization. Once eligibility has been determined, designated study staff will randomly assign participants to a study condition, using the REDCap electronic database.

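### The stated requirement of 458 rests on a clinic ICC inflation that does not fit individual randomisation, and 512 cannot be split equally over three clinics and 16 conditions

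*Protocol article*

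**What the plan says.** All of the following is in the protocol article.

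- **Sample size** gives the inputs: "using the baseline HIV viral suppression rate of 60%, endline rate of 74"%, "a two-sided alpha of 0.05 and 80% power", and an "intraclass coefficient component (ICC) of 0.15, we calculated that we will need a sample of 458".
- The same section justifies the ICC. It concedes that "we do not know the ICC for each clinic to inform the design stage" and continues that "we conservatively assumed they are 0.15, based on recent studies showing ICC estimates ranging between 0.01 and 0.12". Neither a design-effect formula nor a cluster size is given.
- It then allows for up to 10% loss, reaching 510, "which we increased to 512 to be able to sample an equal number of participants across three clinics and 16 study conditions".
- **Randomization** assigns individual participants from the three clinics to the 16 conditions "using a permutation allowing for the study conditions to include an equal number of participants, which is 32". It mentions no stratification by clinic.
- **Eligibility criteria** says "We aim to enroll 512 participants (roughly 170 per clinic").
- **Data and statistical analysis** counts a missing viral load as detectable, analyses all 512 as randomised, and accounts for facility through an exchangeable correlation matrix.

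**The concern.** The sample size section is the trial's only quantitative justification for its enrolment. The stated rates, alpha and power do not lead to 458, and the step that bridges the gap is a clinic ICC. Such an ICC inflates the sample when whole clinics are allocated to arms. Here individuals are allocated, and each clinic contributes to both levels of every component. Describing 0.15 as a cautious choice therefore offers reassurance that it cannot give.

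What is at stake is whether the published power statement describes this trial. If 458 is not the number for 80% power, readers and the DSMB do not know what margin the trial has, in particular once missing viral loads are counted as failures.

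Separately, the reason given for rounding up to 512 can be checked by division, and it fails.

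**Working it through.** **Inputs.** p1 = 0.60, p2 = 0.74, alpha 0.05 two-sided, power 80%, ICC 0.15, loss up to 10% (Sample size); three clinics (Study setting); 32 per condition (Randomization). In Table 2 each component is at its on or enhanced level in 8 of 16 equal conditions, so each main effect is a 1:1 comparison of 256 with 256 at enrolment.

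**1. Requirement without an ICC.** Pooled two-proportion formula, mean rate 0.67:

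n per level = [1.96 x √(2 x 0.67 x 0.33) + 0.8416 x √(0.60 x 0.40 + 0.74 x 0.26)]² / 0.14² = (1.3033 + 0.5534)² / 0.0196 = 175.9, rounded up to 176.

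Total 352. With continuity correction, 190 per level, total 380.

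**2. Reproducing 458.** The implied inflation is 458/352 = 1.301. Solving 1 + (m - 1) x 0.15 = 1.301 gives m = 3.01, the number of clinics. Forwards: 352 x 1.30 = 457.6, rounded up to 458 (229 per level). The next step also follows: 229/0.9 = 254.4, rounded up to 255 per level, total 510.

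Alternatives tried:

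| Base and factor | Total |
|---|---|
| 352, m = 2 (same as 1 + ICC) | 405 |
| 352, m = 10.67 | 863 |
| 352, m = 16 | 1,144 |
| 352, m = 32 | 1,989 |
| 352, factor 1/(1 - ICC) | 414 |
| 380, m = 2 | 437 |
| 380, m = 3 | 494 |
| 380, factor 1/(1 - ICC) | 447 |
| Unpooled 346.3, m = 3 | 450 |
| Arcsine 350.5, m = 3 | 456 |

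None gives 458.

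**3. Does a clinic ICC belong here?** Split the outcome variance into a clinic part, ICC x σ², and a within-clinic part, (1 - ICC) x σ². When each clinic supplies participants to both levels of a component, its clinic effect enters both means and largely cancels in the difference. The variance factor for the contrast is then about 1, or about 1 - 0.15 = 0.85 after adjustment for clinic. It is not above 1. Chance imbalance between clinics is small on average, and the analysis accounts for facility. Only variation of the component effect between clinics would add variance, and an outcome ICC does not measure that.

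**4. Power on the stated rates, complete data.**

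- 229 per level (458): z = (0.14 x √229 - 1.3033) / √0.4324 = (2.1186 - 1.3033)/0.6576 = 1.240, power 89%.
- 256 per level (512): z = (2.2400 - 1.3033)/0.6576 = 1.424, power 92%.

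**5. Power under the primary missing-data rule.** Assume 10% loss in both levels, all coded as detectable. The rates become 0.9 x 60% = 54% and 0.9 x 74% = 66.6%, a difference of 12.6 points with mean 0.603.

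- n per level for 80% power = (1.3562 + 0.5775)² / 0.126² = 235.5, about 471 randomised in total.
- 256 per level: z = (0.126 x 16 - 1.3562) / √(0.54 x 0.46 + 0.666 x 0.334) = 0.6598/0.6862 = 0.962, power 83%.

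Over the plan's range of up to 10% loss, the power of 512 therefore runs from 92% (no loss) to 83% (10%, equal).

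**6. The reason for 512.** 512/16 = 32, as Randomization says. But 512/3 = 170.67 and 512/(3 x 16) = 10.67. Equal numbers over clinics and conditions need a multiple of 48; the nearest are 480 and 528.

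**The case against.** **The mechanism is inferred.** The article names its software and inputs but prints no formula. Another route comes close: a matched-pair calculation with correlation 0.15 gives 152.8 pairs, and 152.8 x 3 = 458.4. This stands, so m = 3 should be put as consistent with the figure and not as a fact about what was done. It does not rescue 458, because a matched-pair calculation does not fit an unpaired comparison either.

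**The harm is small.** The error enlarges the trial. Much of the apparent surplus is then absorbed when missing viral loads count as detectable, since about 471 are needed under 10% equal loss. This also stands. It means that 352, or power of 89% to 92%, should not be presented as the position of the primary analysis.

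**The 512 clause is minor.** The allocation text already gives 32 per condition, and the eligibility text only an approximate number per clinic. That is fair: one clause is wrong and the operative allocation is not.

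**Stronger readings a reader might infer:**

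- That the correct cluster size, about 153 per clinic, belongs in the design effect and the trial is short by thousands. The article does not randomise clinics, so that design effect does not apply. Holding 153 per clinic while the total grows would also imply many more clinics than the three there are.
- That randomisation is stratified within clinic. The Randomization section describes a single permutation balanced over conditions and does not say so.

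**Conclusion.** The statement that 458 participants are needed for 80% power is wrong as written. On the plan's own rates, alpha and power, 352 analysed participants suffice (380 with continuity correction). The extra 30% comes from an ICC adjustment that fits neither the individual randomisation nor, if the inferred m = 3 is right, the design-effect formula. The claim that 512 permits equal numbers across three clinics and 16 conditions is arithmetically false.

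The consequence is limited. The trial is not underpowered for component main effects on the stated assumptions, and neither enrolment nor any estimate changes. The power of 512 is about 83% under the primary rule with 10% loss and 92% with no loss. These figures rest on the plan's 60% and 74%, loss that is equal in both levels, and a component effect that does not vary between clinics. The section should be corrected, but this is a fault in the justification and not in the conduct of the trial.

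**What to change.** In the Sample size section:

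- Delete the ICC inflation and the description of 0.15 as a conservative assumption.
- State that individuals are randomised across the three clinics and that facility is accounted for in the analysis. Do not claim stratification by clinic unless it was done.
- Give 352 as the number for 80% power with complete data. Restate the power of 512 under the missing-as-detectable rule: about 83% for 60% versus 74% with 10% loss equal in both levels.
- Replace the clause on equal numbers across clinics and conditions with 32 per condition and about 170 per clinic.

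The cost is rewording only. Enrolment, allocation and analysis stay as they are.
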